## Abstract

**Background:**

While electronic cigarettes are forbidden in several countries, their sales are exploding in many others. Although e-cigarettes have been proposed as long-term substitutes for traditional smoking or as a tool for smoking cessation, very scarce data are available on their efficacy and safety.

We describe the protocol of a 5-year multicentric prospective study aimed to evaluate short- and long-term adherence to e-cigarette smoking and the efficacy of e-cigarettes in reducing and/or quitting traditional cigarette smoking. The study will also compare the health effects of electronic vs traditional vs mixed cigarette smoking.

**Methods/design:**

From June to December 2013, we will enroll adult smokers of: (EC) e-cigarettes (self-reported inhaling ≥ 50 puffs per week since ≥ 6 months); (TC) traditional cigarettes (≥ 1 per day since ≥ 6 m); (Mixed) both electronic and traditional cigarettes (≥1 per day since ≥ 6 m). Eligible subjects will be requested participation through newspaper advertisements and direct contact at the shops. Each subject will have to compile a structured questionnaire at enrolment and after 6, 12, 24, 36 and 60 months. The level of carbon monoxide in expired after breath will be evaluated in all subjects declaring no traditional cigarette smoking in any follow-up phase, using portable carbon monoxide analyzers. The primary outcomes are traditional smoking cessation rates and number of smoked cigarettes. Secondary outcomes include adherence to e-cigarettes, self-reported adverse events, quality of life, and time to hospital admission for one among cardiovascular diseases, chronic obstructive pulmonary diseases, cancer of the lung, esophagus, larynx, oral cavity, bladder, pancreas, kidney, stomach, cervix, and myeloid leukemia. Admissions will be checked using official discharge data of the Abruzzo Region. A minimum of 500 subjects in each group will be enrolled, for a total of 1500 participants. Cox proportional hazards analysis will be used to calculate adjusted relative hazards of smoking cessation by each variable.

**Discussion:**

Data on long-term efficacy and safety of e-cigarettes will be of utmost importance to form the basis for guidelines and regulatory decisions on e-cigarettes.

**Trial registration:**

The protocol has been registered (NCT01785537) and approved by the Ethics Committee of the University of Chieti (Record n. 6; 25-03-2013).

## Background

The electronic cigarette (e-cigarette) market has been exploding over the past few years, reaching an estimated $500 millions during 2012 in USA; an expected $1 billions by the end of 2013 [1,2]; and achieving similar growth in some European countries [3,4]. Indeed, people report buying e-cigarettes to help quit smoking, to reduce cigarette consumption, to relieve tobacco withdrawal symptoms due to workplace smoking restrictions and to continue to have a ‘smoking’ experience but with reduced health risks [5]. As a matter of fact, e-cigarette is becoming a social phenomenon of global proportion [6,7], which calls for research, legislation and product development [8,9].

Although the product has been proposed as a long-term substitute for traditional smoking or as a tool for smoking cessation [10,11], some authorities are opposing the recreational use of nicotine because there are concerns about both safety and efficacy, and about the potential risk of e-cigarettes to play as a promoter of smoking for never or ex-smokers [10,12-14]. In fact, the sale of e-cigarettes market is subject to limitations in many countries (i.e. USA and Germany) and is forbidden in several others (i.e. China, Brazil) [14].

To date, twelve studies were started evaluating the acceptability, safety or efficacy of e-cigarettes containing nicotine [5,15-25]; seven were completed [16-21,24], and only four have been published [16,17,24,26]. Although the results are encouraging, they are based upon a total sample of <300 subjects, who were followed for no more than 6 months. No data are available on long-term efficacy and safety and, most importantly, no ongoing study has been designed to collect data on hard outcomes (smoking-related cancer, major cardiovascular events and chronic obstructive pulmonary disease – COPD) over a long follow-up period [11,24].

The main aims of the study are to evaluate for the first time the long-term adherence to e-cigarette smoking and the efficacy of e-cigarettes in reducing and/or quitting traditional cigarette smoking. As secondary aims, the study will also evaluate the long-term safety (in terms of smoking-related serious diseases requiring hospitalization) of e-cigarette smoking, comparing its health effects with those of traditional cigarette smoking and mixed electronic and traditional cigarette smoking. We will evaluate over a 5-year follow-up the number of smoking-related hospitalizations, the self-reported quality of life, and the reported adverse events according to current and past smoking habit.

The present paper describes the research protocol of the project, which is currently on course (NCT01785537).

## Methods/design

### Study design and population

This is an observational, prospective cohort study. None of the participants will receive an indication about which product to smoke. In fact, all participants will receive structured flyers reporting the main harms of cigarette smoking.

An individual will be considered for participation if:

– resident in Italy;

– aged between 30 and 75 years;

– smoker of e-cigarettes (inhaling at least 50 puffs per week) since six or more months (EC Group);

– smoker of at least one traditional cigarette per day since six or more months (TC Group);

– smoker of both electronic and traditional cigarettes (at least one per day) since six or more months (Mixed Group).

Exclusion criteria will be:

– illicit drug use,

– breastfeeding or pregnancy,

– major depression or other psychiatric conditions,

– severe allergies,

– active antihypertensive medication,

– angina pectoris,

– past episodes of selected smoking-related major diseases (myocardial infarction, stroke/TIA, congestive heart failure, COPD, cancer of the lung, esophagus, larynx, oral cavity, bladder, pancreas, kidney, stomach, cervix, and myeloid leukemia).

Potentially eligible subjects will be requested participation through newspaper and internet advertisements, through direct contact with an investigator at the shops, finally through direct contact with some of the general practitioners of the Abruzzo Section of the Italian Scientific Society of General Medicine (SIMG) who voluntarily participate to the project. Specific agreements will be established with the sellers to permit the presence of an investigator during conventional working hours. Inclusion and exclusion criteria will be self-reported and further verified by the investigator in case of participation.

The enrolment period will last from June to December 2013. Each subject will be requested to compile a structured questionnaire at the time of enrolment at after 6, 12, 24, 36 and 60 months (and eventually, in the case of an expansion of the follow-up, at 84 and 120 months). After the first contact, the follow-up questionnaires will be compiled through a phone interview or through a specifically created website (http://www.ipazienti/fumo), with private password. To reduce potential misclassification, the level of carbon monoxide in expired after breath will be evaluated in all subjects declaring no traditional cigarette smoking in any phase of the follow-up, using portable carbon monoxide analyzers (Smokerlyzer ® piCO + ™, Bedfont Scientific Ltd.). Such an assessment will be made by the investigators, after specific periodical calibration, directly at the home of the participant or at the office of his/her general practitioner. Among the methods to monitor self-reported smoking cessation, also the assessment of cotinine in saliva can be made using portable and relatively economical devices, and such test showed a slightly higher sensitivity/specificity than tests based upon exhaled CO [27]. However, we were not able to find a seller of cotinine portable tests on saliva, and the measurement of breath CO still showed high levels of sensitivity (>90% [27,28]).

Each participant will have to sign a written informed consent. The study protocol has been registered in Clinicaltrials.gov (NCT01785537) and approved by the Ethics Committee of the University of Chieti (Record n. 6; 25-03-2013).

Participants will be enrolled at various study sites within the Abruzzo and Lazio Region using the same standardized procedures.

All the subjects that will be excluded because of past episodes of selected smoking-related major diseases will be requested to participate into a nested case–control pilot study, in which we will collect hospital admission data retrospectively and compare the rates of smoking-related diseases according to the present and past smoking habits.

### Interventions and groups

This is a non-interventional observational study. The participants will be divided into three cohorts/groups according to their self-determined smoking pattern:

– Group EC - smokers of e-cigarettes only (who are not smoking traditional cigarettes). This group will be further split in the analysis: never or former smokers of traditional cigarettes; smokers of e-cigarettes with or without nicotine.

– Group TC - smokers of traditional cigarettes only. This group will be further split in the analysis: recent and older smokers.

– Mixed Group - smokers of both traditional and electronic cigarettes. This group will be further split in the analysis: mixed smokers who quit and who did not quit traditional cigarette smoking during follow-up.

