### Secondary outcomes

1. Adherence to e-cigarette smoking: number of months of continued e-cigarette smoking in groups EC and Mixed.

2. Traditional and electronic smoking (overall smoking) cessation: percentage of subjects in all groups reporting sustained smoking abstinence from both traditional and electronic cigarette smoking at 6, 12, 24, 36 and 60 months. Smoking abstinence is defined as complete abstinence from tobacco or electronic smoking (not even a puff) for the 30 days period prior to the visit.

3. Time to hospital admission for one of the followings: cardiovascular diseases, chronic obstructive pulmonary diseases, cancer of the lung, esophagus, larynx, oral cavity, bladder, pancreas, kidney, stomach, cervix, and myeloid leukemia. Repeated admissions of the same subject will be counted once and the subject will be censored at the date of the first admission.

4. Rate of subjects with smoking-related hospitalizations: percentage at 1, 2, 3 and 5 years of subjects who had a hospital admission for one of the followings: cardiovascular diseases, chronic obstructive pulmonary diseases, cancer of the lung, esophagus, larynx, oral cavity, bladder, pancreas, kidney, stomach, cervix, and myeloid leukemia. Repeated admissions of the same subject will be counted once.

5. Number of smoking-related hospitalizations: mean number at 1, 2, 3 and 5 years of hospital admissions for one of the followings: cardiovascular diseases, chronic obstructive pulmonary diseases, cancer of the lung, esophagus, larynx, oral cavity, bladder, pancreas, kidney, stomach, cervix, and myeloid leukemia. Each admissions of the same subject will be counted.

6. Number of hospitalizations for cardiovascular diseases: mean number at 3 and 5 years of hospital admissions for cardiovascular diseases. Each admissions of the same subject will be counted.

7. Number of hospitalizations for smoking-related cancers: mean number at 3 and 5 years of hospital admissions for cancer of the lung, esophagus, larynx, oral cavity, bladder, pancreas, kidney, stomach, cervix, and myeloid leukemia. Each admissions of the same subject will be counted.

8. Self-reported quality of life: average quality of life according to EuroQoL EQ-5DL at 6, 12, 24 and 36 months. The analysis of quality of life will follow the technical specifications recommended by the EuroQol group [29].

9. Reported side effects at 6, 12, 24, 36 and 60 months.

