### Data analysis

All data will be collected and initially handled by the Coordinating unit, which is responsible for privacy regulations and maintains the property.

At each time-point, the differences in the rates of traditional smoking cessation (or other categorical outcomes such as adverse events) across groups will be first examined using Fisher’s exact test. Cox proportional hazards analysis will be used to calculate the adjusted relative hazards of traditional smoking cessation (and smoking-related hospitalization) by each variable. Stochastic level of entry into the model will be set at 0.10, with age, gender, and smoking groups forced to entry, and multicollinearity, interactions with time to event and higher-power terms will be explored for all variables in the final model. A minimum events-to-variable ratio of 10 will be maintained in multivariate modeling to avoid overfitting, and Schoenfeld’s test will be performed to check the validity of proportional hazards assumption. Kaplan-Meier survival analysis will also be used to examine the association between hospitalization and smoking group. The validity of constant incidence ratios over the follow-up will be checked using Nelson-Aalen cumulative hazard estimates.

Multiple linear regression will be used to investigate the predictors of the difference in the number of traditional cigarettes smoked between baseline and each time-point of follow-up. Additional multivariate models such as mixed-effect logistic models will be explored for both the primary and secondary outcomes to account for repeated observations and the potential distortions of the variability in the exposure to traditional cigarette smoking by the participants in groups EC and Mixed (for which also stratification will be considered) [31]. In all mixed models, the cluster variables will be participant’s id, nicotine level of the electronic and traditional cigarette and exposure to past traditional cigarette smoking. We will assume and independent correlation structure for all clusters, but we will also repeat all models setting an exchangeable correlation structure.

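### The Mixed group is split by quitting during follow-up; used as a fixed grouping for hospitalization, that split is open to immortal-time or sick-quitter bias

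*Protocol article*

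**What the plan says.** Interventions and groups forms three cohorts by smoking pattern at enrolment and announces further splits. The EC and TC splits read as baseline features: past tobacco smoking, nicotine content, recent or older smoker. The Mixed split is different: "This group will be further split in the analysis: mixed smokers who quit and who did not quit traditional cigarette smoking during follow-up". No outcome is named for it.

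The end of the Background says the study will evaluate "the number of smoking-related hospitalizations, the self-reported quality of life, and the reported adverse events according to current and past smoking habit". Secondary outcome 3 is time to a smoking-related admission, with the rule "Repeated admissions of the same subject will be counted once and the subject will be censored at the date of the first admission". Secondary outcomes 4 to 7 are percentages and mean counts of admissions at fixed years.

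For the models, Data analysis states: "Cox proportional hazards analysis will be used to calculate the adjusted relative hazards of traditional smoking cessation (and smoking-related hospitalization) by each variable", "with age, gender, and smoking groups forced to entry". It adds: "Kaplan-Meier survival analysis will also be used to examine the association between hospitalization and smoking group". Quitting is judged from the 30 days before each visit at 6, 12, 24, 36 and 60 months (Primary outcomes).

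**The concern.** Admissions are counted from enrolment, but a Mixed participant becomes a quitter only later. If that later status labels the whole follow-up, two errors are possible, and they run in opposite directions.

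- **Immortal time.** If a quit counts only when it precedes the first admission, everyone labelled a quitter was admission-free up to the quit. That event-free time is credited to quitters, who look protected.
- **Sick quitting.** If a quit counts whenever it occurs, people who stop smoking because they were admitted become quitters, and their admissions go with them. Quitters look harmed.

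Long-term safety by smoking pattern is a stated secondary aim, and the Discussion intends the results to inform guidelines and regulation. Whether dual users who give up tobacco are admitted less often is a question readers will take from this split.

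**Working it through.** **The plan's own figure.** The only calculation in the article that uses a Mixed quit rate is the sample size for 20% v 30% cessation at 5 years. With two-sided alpha 0.05 and 80% power:

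n = [1.960 × √(2 × 0.25 × 0.75) + 0.842 × √(0.16 + 0.21)]² / 0.10² = 293.2, so 294.

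With continuity correction, (293.2/4) × [1 + √(1 + 4/(293.2 × 0.10))]² = 312.8, so 313. This is the stated number. The article gives no figure for the quitter comparison, so what follows is a calculation under no true effect.

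**Inputs.** From the article: 30% quitting by T = 5 years (Sample size estimation) and the visit times. Assumed: constant quit hazard; constant admission hazard h, the same for all, at 0.5% to 2% per year; share s of admissions that prompt quitting. The quit hazard is q = −ln(0.70)/5 = 0.0713 per year, and F(t) = 1 − exp(−qt) is the share who have quit by t. The formulas below are the limit for small h. Per participant, total follow-up is then 0.30 × 5 = 1.5 years for those labelled quitters and 0.70 × 5 = 3.5 years for the others.

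**A. Quits count only before first admission, exact dates.** Average time after quitting is 5 − 0.30/0.0713 = 0.794 years, and time not yet quit is 4.206 years. Admissions before a quit fall to non-quitters.
- Quitter rate: 0.794h/1.5 = 0.530h
- Non-quitter rate: 4.206h/3.5 = 1.202h
- Ratio: 0.44

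**B. As A, but the quit is dated to the visit that records it.** F(0.5) = 0.035, F(1) = 0.069, F(2) = 0.133, F(3) = 0.193. Time after a recorded quit is 0.035 × 0.5 + 0.069 × 1 + 0.133 × 1 + 0.193 × 2 = 0.605 years.
- Quitter rate: 0.605h/1.5 = 0.403h
- Non-quitter rate: 4.395h/3.5 = 1.256h
- Ratio: 0.32

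**C. Quits count over all 5 years and a share s of admissions prompts quitting.** Ratio = (0.30 + 0.70s) / [0.30 × (1 − s)].
- s = 0: 1.00
- s = 0.10: 0.37/0.27 = 1.4
- s = 0.20: 0.44/0.24 = 1.8
- s = 0.40: 0.58/0.18 = 3.2

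**Simulation check.** Cox hazard ratios, 1,000,000 subjects per scenario, 30% quitting, no true effect:

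| Admission hazard per year | A | B | C, s = 0 | C, s = 0.20 | C, s = 0.40 | Time-updated (rate ratio) | 1-year landmark |
|---|---|---|---|---|---|---|---|
| 0.5% | 0.45 | 0.32 | 1.01 | 1.82 | 3.20 | 1.02 | 1.02 |
| 1% | 0.44 | 0.32 | 1.00 | 1.80 | 3.11 | 1.00 | 0.99 |
| 2% | 0.44 | 0.33 | 1.01 | 1.79 | 3.02 | 1.00 | 1.00 |

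The ratios hardly move with the assumed admission hazard. Widening to 20% to 40% quitting and hazards of 0.5% to 4% gives 0.42 to 0.46 for A, 0.31 to 0.35 for B and about 1.5 to 4.2 for C with s of 0.20 or 0.40. Over that same range, time-updated status gives 0.96 to 1.03 and the landmark 0.97 to 1.04. The time-updated and landmark runs do not include admission-prompted quitting.

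**The case against.** The strongest reply is that the link to hospitalization is inferred. The sentence on the split names no outcome, and the Cox and Kaplan-Meier sentences speak of smoking groups, which the article defines as EC, TC and Mixed. A condensed article may also leave the handling of quit dates to an analysis plan. The aim to analyse by current and past habit is compatible with an updated exposure, and Data analysis acknowledges that exposure to tobacco varies in EC and Mixed. This stands in part, and it is why the point is conditional. It does not remove the point: the article fixes a grouping by a later event, and none of its stated remedies repairs a time-to-event comparison. Mixed-effect logistic models clustered on participant do not move pre-quit time to the right category, stratifying on eventual quitting repeats the problem, and interactions with time test a changing effect, not a changing exposure.

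Second, the low ratios need quit recording to stop at first admission. The rule "the subject will be censored at the date of the first admission" belongs to secondary outcome 3, while questionnaires are due from every participant to 60 months. That is right, and it makes case C the more literal reading. Case C is unbiased only if admissions for infarction, stroke, COPD or cancer never prompt quitting and those lost after admission are still classified. The article itself expects 20% withdrawals or dropouts.

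Third, events are few. At an assumed 1% per year, 500 × (1 − exp(−0.05)) gives about 24 first admissions in Mixed, some 7 of them (30%) among quitters if quitting and admission are unrelated. This limits what any quitter analysis can show, but does not make a biased one acceptable.

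A reader might also infer three stronger claims, none of which the article supports:
- That the main safety comparison is biased. It uses enrolment groups, which this split does not touch.
- That the split contaminates the primary analyses. Sample size estimation defines both, and neither uses it.
- That TC participants who take up e-cigarettes are wrongly kept in TC. The article does not say how they are handled.

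**Conclusion.** The point holds in conditional form. The article commits to splitting Mixed by an event after enrolment and gives no time-updating, landmark or ordering of quits before admissions. If that split is carried as a fixed grouping into secondary outcomes 3 to 7, the comparison of quitters with non-quitters, or of either subgroup with EC or TC, is not interpretable. With no true effect, the ratio could be about 0.3 to 0.4 or about 1.8 to 3.1, depending on a dating rule that the article does not state. The 30% quit rate is the article's; the admission hazards and the shares of admissions prompting quitting are assumptions. Because the two biases oppose each other, no net direction can be claimed.

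**What to change.** State which outcomes the Mixed split serves. For hospitalization:

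- **Cox model.** Treat quitting in Mixed as a time-varying exposure updated at each questionnaire: non-quitter person-time until the visit that records the quit, quitter person-time afterwards. Repeat with a one-visit lag as a sensitivity analysis for sick quitting.
- **Kaplan-Meier curves and secondary outcomes 4 to 7.** Show them by quit status only from a landmark visit, for example 12 months, with status fixed at that visit and only later admissions counted.

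The comparison by enrolment group stays as planned. Smoking habits are already asked at each questionnaire, so no new data are needed.

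The cost is programming and some lost information. At the assumed 1% per year, a 12-month landmark drops about 500 × (1 − exp(−0.01)) = 5 of the 24 or so first admissions. It leaves about 500 × 0.069 = 34 quitters at that visit, and the 1-year figures can no longer be shown by quit status. The landmark displays would therefore be descriptive, with the time-varying model as the main analysis of quitting.

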### Questionnaire

The structured questionnaire is available as online supplementary material and contains questions on demographic data (gender, age, height and weight, educational level, marital status, occupation), previous diseases which are and are not among the reasons for the exclusion, smoking habits, smoking related diseases which did or did not require hospitalizations (only in follow-up assessments), lifestyle behavior (physical activity, alcohol use) and quality of life. The latter issue will be investigated using the Italian version of the validated EuroQol EQ-D5L questionnaire [29]. The questionnaire will be kept as short as possible to allow phone interviews and will be initially tested on a sample of 50 participants to assess acceptability, exclude potentially redundant or include potentially useful questions.

